#### 2.4.3. Anthropometrics Assessment

These measurements will be taken by a researcher with extensive experience in anthropometric procedures. This will not only ensure greater intra-observer reliability, as these measurements will be taken by a single measurer, but will also eliminate the risk of inter-observer errors. The height will be measured using a stadiometer with a scale of 0.0 to 210 cm, while the children are barefoot and wearing only essential clothing (shorts and t-shirts). The Body weight will be measured using bioimpedance on a Tanita MC-780MAS Segmental digital scale (Tokyo, Japan). The body weight and height data will be used to calculate the Body Mass Index (BMI) using the formula BMI = Weight/(height)^2^.

#### 2.4.4. Motor Competence Assessment

Motor competence will be assessed using the KTK3+ test battery [28], which is an adaptation of the original Körperkoordinationstest für Kinder (KTK) by Kiphard and Schilling [21].

The original KTK primarily assesses gross motor coordination through balance and locomotor tasks; however, the KTK3+ introduces an additional eye–hand coordination (EHC) task, thereby expanding its capacity to evaluate manipulative skills, a core component of motor competence. This makes the KTK3+ a more holistic and ecologically valid tool, aligning with the theoretical frameworks that define MC as comprising locomotor, stability, and manipulative components [29,30].

The use of KTK3+ is therefore methodologically strategic, as it will allow us to comprehensively assess the multidimensional impact of both a mono-athletic sport and enriched athletic training program on children’s MC.

##### KTK3+ Test Application and Procedures

The test is made up of four tasks: Task 1, balancing backwards (BB); Task 2, jumping sideways (JS); Task 3, moving sideways (MS) [31]; and Task 4, eye-hand coordination (EHC). According to Gorla et al. [32], in the first task, dynamic balance is mainly checked; in the second, lower limb strength; in the third, laterality and spatial–temporal structuring; and in the fourth, locomotion, balance, and object control.

In the BB task, there are three trials per balance beam, which decrease in width as the test progresses (6.0 cm to 4.5 cm to 3.0 cm). The total number of steps is counted, with a maximum of 72 steps (or 8 steps in each trial per balance beam).

In the JS task, participants have to jump with two feet over a wooden slat for 15 s. The final score results from the sum of the number of jumps in both trials.

In the MS task, participants have to move sideways on a straight-line handling two wooden platforms for 20 s. The total score results from summing the number of times the participants put down a wooden platform and the number of times the participants step on the displaced wooden platform during both trials.

The EHC test is a valid and reliable product-oriented test [28] that determines the level of control of a tennis ball while conducting repetitive movements (i.e., left hand throw, right hand catch, followed by right hand throw, and left hand catch, etc.) as frequently as possible in a time-constrained task of 30 s [33]. The participants are free to use overhand and/or underhand techniques or a combination of both for throwing and catching. For this purpose, participants have to stand 1 m from a wall and throw the tennis ball at eye-level within a square (1 m^2^) taped on the wall, with the bottom side of the square 1 m above the ground. Participants perform this test twice, with the number of successful ball catches across both trials resulting in the test score.

The results of each item are compared with the normative values provided by the authors, and each item is assigned a quotient. The sum of the four quotients represents the global motor quotient (GMQ), which can be presented as a percentage or absolute value, making it possible to classify children for each age and sex according to their level of coordination development. For the total KTK3+ MQ-score, a classification of 5 levels of MC based on the normal distribution can be made [34]: (i) values below 70 are seen as an indicative of “severe gross MC disorder”; (ii) values between 71 and 85 are considered to represent “moderate gross MC disorder”; (iii) values between 86 and 115 are seen as “normal gross MC proficiency”; (iv) values between 116 and 130 are seen as “good gross MC proficiency”; and (v) values above 131 point to “high gross MC proficiency”. Before the initial assessment there will be practitioner training of the research team that will be assessing the KTK3+ to assure high inter-rater reliability.

### 2.5. Study Protocol

The protocol for both groups will be conducted according to the SR [35]. The subjects will be familiarized with the different exercises and tests during the preceding training period. The body composition and MC parameters will also be assessed at baseline (pretest) and post-intervention.

#### 2.5.1. Training Programs

The training programs will be implemented in both groups over 12 consecutive weeks, with 60 min training sessions three times a week, at Leiria’s Main Stadium, [name]. The coaches will monitor the children’s attendance and absences at the training sessions, recording them on a specific attendance sheet.

##### Intervention Group A (IG_A) Training Program

Intervention Group A (IG_A) will participate in structured athletics training sessions three times per week, each lasting 60 min. The sessions will be held at the Municipal Stadium of Leiria—[name]—on Tuesdays and Thursdays from 17:30 to 18:30, and on Saturdays from 09:00 to 10:00. The structure of each session will follow a consistent format. (i) Warm-up (5 min): Dynamic stretching or light jogging. (ii) Main phase (45 min): Focused athletics training targeting specific objectives—technique, speed, strength, and endurance. (iii) Cool-down (5 min): Static stretching or light jogging. The participants in this group will engage exclusively in athletics training, with no additional activities. The detailed 12-week training program is presented in Table 1.

Training Components OverviewRunning and technique Training

This component focuses on enhancing the biomechanics and efficiency of running. Exercises include drills with and without equipment (e.g., cones, hurdles, pins, and ropes) to promote better posture, stride mechanics, and coordination.

Speed Training

Speed sessions emphasize velocity over short distances (10–30 m), reaction starts, and agility circuits. Activities include varied start positions (sitting, lying), slalom runs, and hurdle sprints to improve explosive acceleration and coordination.

Strength Training

Strength development will be primarily based on bodyweight resistance exercises (e.g., planks, squats, and jumping jacks) and light resistance tools (e.g., 1–2 kg medicine balls, ropes, and kettlebells). Training will follow a circuit-based format using Tabata intervals (20 s work, 10 s rest). Each session will include 4–5 rounds of 4 exercises, with 2 min rests between rounds, focusing on proper technique, functional strength, and muscular endurance.

Resistance Training

Endurance activities will be integrated through continuous running (12–15 min) and structured motor games (e.g., relays, object transport tasks, and team challenges). Given children’s limited motivation for isolated endurance drills, the activities are designed to be engaging and enjoyable, promoting a long-term affinity for aerobic exercise.

##### Intervention Group B (IG_B) Training Program

Intervention Group B (IG_B) will be engaged in three weekly training sessions, each lasting 60 min. The sessions will take place at the Municipal Stadium of Leiria—[name]—on Tuesdays and Thursdays from 18:30 to 19:30, and on Saturdays from 10:00 to 11:00. This group will follow a blended training approach: (i) two sessions per week (Tuesdays and Saturdays) focused on athletics, replicating the exact training content as IG_A; (ii) one weekly session (Thursdays) dedicated to complementary motor activities, alternating between gymnastics, handball, swimming, and motor games. The complementary session is strategically scheduled for Thursdays, a day with normally higher attendance and positioned between the two athletics sessions, to ensure optimal participation and recovery. A detailed breakdown of the 12-week program is provided in Table 2.

*Training Objectives*

The IG_B program is designed to evaluate the impact of combined athletics and multi-sport exposure on motor competence development. This group will receive the same foundational athletics training as IG_A, but with an added component of diversified motor experiences. The goal is to determine whether this combined training model will provide greater MC benefits than an athletics-only approach.

*Complementary Activities*

*Gymnastics and handball*

These sessions will emphasize foundational movement skills (FMSs) rather than technical sport-specific mastery. The intent is to expose participants to a variety of motor patterns through basic posture, balance, coordination, object manipulation, jumping, and rolling tasks. In handball, an emphasis will be placed on ball handling, passing, receiving, and spatial awareness, helping to enrich motor diversity.

*Swimming*

In week 10, swimming will be introduced to develop aquatic motor skills, including propulsion and object manipulation in water. This aims to broaden the scope of physical literacy and neuromuscular adaptation through exposure to aquatic environments.

*Motor games*

Motor games will be employed to stimulate key motor competencies, such as locomotion, coordination, balance, and object manipulation. These games are intentionally chosen for their educational value and children’s familiarity with them, ensuring engagement and effective skill acquisition. Activities will include cooperative games, relay formats, object transport tasks, and dynamic obstacle circuits.

## 3. Outcomes

The assessments will be conducted at the Main Stadium of Leiria, [name]. We will use a gym prepared for gymnastics training. It is a large, well-equipped space that provides an atmosphere of concentration and comfort during testing. The MC assessment will occur on a Tuesday (i.e., three days after the last session—Saturday). In addition, assessments will take place during the training session period, meaning that IG_A will be tested at 17h30 and IG_B at 18h30. Given the spatial, human, and material conditions, it is possible for children from the same group to take the tests simultaneously, facilitating the process. Before carrying out the tests, the research group will provide the children with as much information as possible to avoid any doubts and answer all their questions clearly.

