## 2. Materials and Methods

### 2.1. Study Design

This study follows a randomized, controlled experimental design with parallel groups (1:1 allocation ratio), aimed at evaluating and comparing the effects of two types of training protocols on MC in children aged 6 to 10 years. This methodology is used considering the conclusions of the systematic review and the fact that the main researcher is an athletics coach.

The participants will be ecologically assigned into one of two intervention groups, depending upon the training schedule chosen by their parents, according to their availabilities, and being given no prior indication of which of the two programs will function on which schedule: (i) Intervention Group A (IG_A) will receive athletics-based training exclusively, three times per week for 12 consecutive weeks, with each session lasting 60 min; and (ii) Intervention Group B (IG_B) will receive a combined program consisting of athletics-based training twice per week and one additional session per week involving a complementary activity (gymnastics, handball, or motor games), also over 12 weeks and with 60 min sessions.

All the participants will undergo MC assessments at two times: (i) at baseline (T0), prior to the beginning of the intervention; and (ii) at post-intervention (T1), immediately following the 12-week training period.

The post-intervention evaluations will take place three days after the final training session, always in the afternoon, to ensure consistency in the testing conditions. Figure 1 illustrates the participant flow and intervention timeline for the trial.

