## 5. Discussion

The present study sought to examine and compare the effects of two distinct training program interventions on MC in children aged 6 to 10 years, a developmental period recognized as crucial for the acquisition of FMSs and long-term physical literacy [38,39]. As MC has been widely recognized as a key factor in promoting health and well-being and has also been linked to physical health and psychosocial aspects throughout childhood [3], children with higher motor proficiency are more likely to be physically active, creating a positive feedback loop in which motor development facilitates physical activity, and physical activity, in turn, enhances motor skills. Children who develop strong motor skills often report higher levels of self-efficacy, which encourages regular participation in physical and sports activities, contributing to the adoption of healthy lifestyle habits [38].

Grounded in the findings of a preliminary SR [35], we designed two intervention protocols, one based on athletics alone (IG_A) and the other using a complementary sport program to athletics training with a multi-activity structure (IG_B), both aiming to enhance the core components of MC: locomotion, object manipulation, and postural stability [6].

As the main researcher is an athletics coach, our aim with this study was to propose this training methodology for athletics, aimed at the 6–10 age group, to see whether it is feasible to promote the acquisition of sport-specific skills in athletics without compromising the development of MC. It is important to note that the intervention program that will be implemented essentially aims to show that it is possible to achieve better CM results with just one change to one of the weekly training sessions. In addition, it is also important to say that if there are results in this regard, athletics clubs will be challenged to incorporate these complementary activities into their programs.

*Multi-component Design and Theoretical Foundations*

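### Each arm is tested as a block in its own training slot, so the slot shows the arm to scorers who know the timetable, and test hour cannot be separated from programme

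*Protocol article*

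**What the plan says.** Section 3 (Outcomes) sets the MC test on a Tuesday and says that "assessments will take place during the training session period", so that "IG_A will be tested at 17h30 and IG_B at 18h30". The programme descriptions in section 2.5.1 confirm that these are the arms' own training hours: IG_A trains "on Tuesdays and Thursdays from 17:30 to 18:30" and IG_B "on Tuesdays and Thursdays from 18:30 to 19:30". Section 3 adds that "it is possible for children from the same group to take the tests simultaneously"; it does not describe children from different groups being tested together.

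On who scores, the KTK3+ section says that before the first assessment "there will be practitioner training of the research team that will be assessing the KTK3+ to assure high inter-rater reliability". The same section defines all four tasks as counts made by an observer: steps on the beams, jumps, platform placements and steps, and successful catches.

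On expectation, hypotheses iii and iv in the Introduction predict greater improvement in IG_B. The Discussion says the programme "essentially aims to show that it is possible to achieve better CM results with just one change to one of the weekly training sessions". Section 2.1 notes that "the main researcher is an athletics coach".

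Section 2.1 also says that post-intervention testing is always in the afternoon, to keep conditions consistent. It does not equalise the hour between arms.

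**The concern.** Two problems follow from one timetable.

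- **Scoring.** A block of children arriving at 17:30 is IG_A and a block arriving at 18:30 is IG_B. A team member who knows the timetable therefore knows the arm while counting. Most counts are simple, but some need judgement, such as whether a catch was successful. A small shared leaning towards IG_B at T1 would look exactly like a treatment effect. Rater training, the one safeguard described, improves agreement between raters. It does not remove an expectation that they share.
- **Hour.** Every IG_A child is tested at one hour and every IG_B child at another. Time of day, the assessors' tiredness and the atmosphere of the session all go with the arm, and no covariate can separate them.

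At stake is whether a significant result can be attributed to the programme. The six planned analyses all use scores from the same test sessions, so the same bias could enter all of them.

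**Working it through.** The plan gives no figure for this point. The check has three steps: does slot equal arm, which comparisons are exposed, and how much would a given bias matter.

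**1. Slot and arm.** IG_A trains on Tuesdays 17:30-18:30 and is tested at 17:30. IG_B trains on Tuesdays 18:30-19:30 and is tested at 18:30. No crossing or mixing is described. Slot and arm are one variable.

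**2. Which comparisons are exposed.** Let h be a constant effect of the later hour on a score, and b a scoring bias in favour of IG_B at T1 only. With no true effect and equal groups at the start, the expected IG_B minus IG_A differences are:

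| Comparison | Same slots at T0 and T1 |
|---|---|
| Group × time interaction (difference in change) | (h + b) − h = b |
| T1-only comparison (hypothesis ii) | h + b |
| Group main effect (mean of T0 and T1) | h + b/2 |

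So h drops out of the interaction if both assessments use the same slots, and b does not. An hour effect that changes over the 12 weeks would act like b.

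**3. Size.** Inputs from section 4 (Statistical Analysis): 18 per group, r = 0.50, α = 0.05. I take 18 per group as stated. Standard G*Power formulas give 14 per group for the interaction (ε = 0.80) and 32 per group for the between-groups test, so 18 does not reproduce. That is a separate matter and does not alter this point.

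For the interaction, in units of the SD of a single score:

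- SD of change = √(2(1 − 0.50)) = 1.00
- SE of the difference in change = 1.00 × √(2/18) = 0.333
- df = 2 × 18 − 2 = 34, two-sided critical t = 2.032
- noncentrality = bias / 0.333

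Because the SD of change is 1.00 at r = 0.50, a T1-only comparison has the same SE and the same rates. For the group main effect, the variance of a child's mean of two scores is (1 + 0.50)/2 = 0.75, so SE = √(0.75 × 2/18) = 0.289.

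Probability of rejecting at nominal 5% with no true effect (noncentral t):

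| Assumed bias (SD) | Noncentrality, interaction | Interaction (bias at T1 only), or T1-only comparison | Group main effect (constant hour effect) |
|---|---|---|---|
| 0.1 | 0.3 | 6.0% | 6.3% |
| 0.2 | 0.6 | 9.0% | 10.3% |
| 0.3 | 0.9 | 14.1% | 17.3% |
| 0.4 | 1.2 | 21.5% | 27.0% |
| 0.5 | 1.5 | 30.8% | 39.1% |

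The 0.4 SD interaction value is 0.2146 before rounding, so about 21%. At 0.05 SD the interaction rate is 5.2%, practically nominal. A larger sample does not help: with 21 per group (18 × 1.15 = 20.7, rounded up), SE = √(2/21) = 0.309, and a 0.3 SD bias gives 15.8% instead of 14.1%.

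**The case against.** The best case for the plan is that the main analysis is a group-by-time ANOVA, and that testing each child at the usual training hour keeps conditions constant within the child. Section 3 speaks of assessments in the plural, which suggests the same slots at T0. On that reading a constant hour effect cancels in the interaction. This stands, and it confines the hour problem to the T1-only comparison, the group main effect and any hour effect that drifts over the 12 weeks. It does not touch scoring bias at T1.

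It is also fair that the tasks leave limited room for bias: three are timed counts, the balance score is capped at 72 steps, and the eye-hand task is described as valid and reliable. This argues for a small bias, not for none. The programme description also states the goal neutrally, as finding out whether the combined model does better.

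A reader might infer more than the documents support:

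- **That every count is known to be scored by someone aware of the arm.** The article never says so. It is a firm inference from the timetable and from the research team doing the scoring, but an inference. Who staffs each station may be set out in the full protocol.
- **That coaches score their own groups.** The article gives the coaches the attendance record and does not place them at a test station. That the main researcher is a coach shows neither bias nor its direction.
- **That assessors encourage children unequally.** The test procedures mention no encouragement. The point rests on the observer's counts alone.
- **That the difference in hour by itself invalidates the interaction test.** It does not, if T0 used the same slots.

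Condensation does not excuse the timetable, which is a rule the article states.

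**Conclusion.** The point holds for the timetable. Separate slots reveal the arm to scorers who know the schedule, and the article describes nothing that offsets this. Expectation at T1 would then load on the interaction, where no analysis can remove it. The hour confounding is complete but narrower in effect: it matters for hypothesis ii and the group main effect, and for the interaction only if the hour effect changes between T0 and T1.

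The size depends on a bias that the documents do not give. Over an assumed 0.1 to 0.5 SD at T1, the false-positive rate of the interaction test runs from about 6% to 31%. At the low end the harm is slight; from about 0.3 SD (14%) it is material. These figures assume 18 per group, r = 0.50, no true effect and a bias in one arm only. The change should be made before T0, since the bias cannot be corrected afterwards.

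**What to change.** Change the test-day timetable in section 3, for T0 and T1 alike:

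- Test both groups on the same Tuesday across 17:30-19:30, with children from both arms mixed in each slot. Let a child keep the usual hour where the family cannot attend the other.
- Record scores by participant number only, with no group on the score sheet.
- Assign existing team members who led neither programme to the scoring stations, as far as possible.
- Keep the same assessor on the same task at both times.

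Sample size, programmes and analysis stay as they are.

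**Cost.** Some families attend an hour earlier or later on two days. Section 2.1 says that parents chose the schedule by availability, so there is a small risk of missed tests, and an incomplete assessment excludes the child under exclusion criterion iv in section 2.2. The option to keep the usual hour limits that risk, at the price of less complete mixing. Masking is only partial where assessors already know the children from the club. Whether extra staff are needed depends on how far the research team overlaps with the coaches, which the article does not state.

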## 4. Statistical Analysis

The required sample size was calculated using the G*Power software (3.1.9.4; Heinrich Heine University Düsseldorf, DE). As the aim is to detect differences in the KTK3+ between the two groups, and considering that the analysis will be performed on the outcomes, a between–within ANOVA-RM (2 [groups] × 2 [time points]) will be conducted, anticipating a ‘large’ effect size (f = 0.4) based on similar previous studies using the KTK3+ [26,27,36], with an α = 0.05, a statistical power of (1 − β) = 0.95, correlated dependent variables with an r = 0.50, and a violation of sphericity (ε) = 0.80. This analysis will require a total sample size of 18 individuals per group. Thus, the study should start with an additional 15% of the planned sample size for each group to account for potential dropouts as suggested by several authors (e.g., [37]). It will also be comparable to previous school-based MC studies that employed the KTK3+ as an outcome measure in early childhood and primary education contexts [24,25], considered adequate for the study objectives and the planned statistical analyses. The means and standard deviation will be calculated for all the studied variables. The normality and homoscedasticity will be verified with the Shapiro–Wilk (n < 50) and Levene’s tests, respectively. The statistical analyses will be conducted in IBM SPSS Statistics version 27. The referred to ANOVA-RM will be applied to each of the four KTK3+ battery tests independently and to the KTK3+ battery results as a whole, namely to its raw results and to its Global Motor Quotient. Thus, we will be conducting six distinct analyses and will extract conclusions from each of them, with the latter two being the most important, as global results. Nevertheless, if specificities can be found for the other four, we intend to address and to consider them.

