Middle childhood, between the ages of 6 and 10, is a critical period for motor skill acquisition, characterized by rapid neuromuscular maturation, growth in physical capacities, and heightened adaptability to training stimuli. The evidence from school- and community-based interventions shows that structured PA (e.g., games, plyometric training, dance, and sports) or aquatics (e.g., swimming) consistently improves FMSs, coordination, and overall MC in this age group [16,17,18]. Aquatic programs have demonstrated significant gains in both global and specific motor skills, even over short durations, while land-based interventions have been shown to enhance complementary domains, such as strength, agility, and locomotor proficiency [19,20]. Collectively, the literature highlights that providing diverse, developmentally appropriate movement experiences during this sensitive growth window not only optimizes motor development but also supports long-term physical literacy and active lifestyle habits.

In this context, it becomes essential to assess the effects of systematic and structured training programs targeting MC development in early school-age children. Standardized tools, such as the Körperkoordinationstest für Kinder (KTK) [21], Test of Gross Motor Development of Ulrich [22], and Motor Assessment Batteries for Children (MABC) of Henderson and Sugden [23], have been widely used to evaluate MC due to their reliability and suitability for children aged 6 to 10 years.

Thus, the aim of this study is to design and evaluate a 12-week athletics-based training program for children aged 6 to 10, assessing its effects on MC. The hypotheses are as follows: (i) There will be significant improvement in MC after the 12-week intervention. (ii) There will be significant between-group differences in MC levels post-intervention. (iii) There will be significant improvement in MC of IG_B group after the 12-week intervention compared to the IG_A. (iv) The multi-activity program will lead to greater MC improvement in the IG_B group.

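### With one training group per programme, the ANOVA-RM compares two particular groups of children, so its 5% error rate does not carry over to a claim about the programmes

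*Protocol article*

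**What the plan says.** Section 4 (Statistical Analysis) fixes the model: "a between–within ANOVA-RM (2 [groups] × 2 [time points]) will be conducted". It is sized "with an α = 0.05, a statistical power of (1 − β) = 0.95", giving 18 children per group plus 15% for dropout. The calculation contains no intraclass correlation, design effect or training-group term.

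Section 2.5.1 gives one timetable per programme. IG_A trains "on Tuesdays and Thursdays from 17:30 to 18:30, and on Saturdays from 09:00 to 10:00"; IG_B trains "on Tuesdays and Thursdays from 18:30 to 19:30, and on Saturdays from 10:00 to 11:00". No second training group is described in either arm. Section 3 (Outcomes) tests IG_A at 17h30 and IG_B at 18h30, and allows children of the same group to be tested at the same time.

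The conclusions sought are about programmes. Hypothesis (iv) in the Introduction reads "The multi-activity program will lead to greater MC improvement in the IG_B group". The IG_B training objectives in Section 2.5.1 ask whether the combined model gives more benefit than athletics alone. The Discussion says that confirmed superiority of the IG_B programme would support policy and curriculum recommendations. Its limitations paragraphs do not mention delivery to one group per arm.

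**The concern.** Over 12 weeks × 3 sessions = 36 sessions, the children of one arm share peers, session delivery and group dynamics, and they are then tested together. Their gains may therefore be correlated. The error term of the group-by-time test contains only variation between children within a group; variation between training groups is implicitly set to zero.

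With one training group per arm, anything that makes one group's sessions or test occasion go better is indistinguishable from an effect of the programme. A rejection could then arise with equally effective programmes, more often than the stated 5%, and be offered to clubs and curriculum planners as evidence for the multi-activity model.

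This is separate from how children enter the groups. Section 2.1 says by the parents' choice of schedule, while Sections 2.2 and 2.4.1 say at random. Even genuine randomisation of children would leave one delivery group per arm.

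**Working it through.** **Inputs from the article.** Two-sided α = 0.05; n = 18 per group; two groups and two time points (Section 4); one training slot per programme (Section 2.5.1). **Assumed input.** The ICC of the change score, ρ. The article gives none, so a range is shown. The change-score ICC is the relevant one because stable baseline differences between groups cancel in the group-by-time contrast.

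**Step 1: the plan's own figures.** With two time points, the group-by-time F test equals a two-sample t-test on change scores with 2 × 18 − 2 = 34 degrees of freedom. With ρ = 0 it rejects 5.0% of the time (5.1% in 40,000 simulated trials), so the nominal level is reproduced when there is no group-level variance. The sample size is not reproduced: with f = 0.4, r = 0.50 and power 0.95, the usual interaction calculation needs 24 children in total (ε = 1) or 28 (ε = 0.80), and the between-group effect needs 64; none gives 36. That is a separate matter, and n = 18 is taken here as stated.

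**Step 2: error rate for a programme claim.** Let each arm's training group add a random effect to its children's gains, with variance ρ, and let the within-group variance be 1 − ρ. With equally effective programmes:

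- true variance of the difference in mean gains = 2[ρ + (1 − ρ)/n];
- variance that the ANOVA-RM estimates = 2(1 − ρ)/n;
- ratio k = 1 + nρ/(1 − ρ), so the true standard error is √k times the reported one;
- true two-sided type I error = P(F(1,34) > F_crit/k), where F_crit is the 5% critical value.

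For ρ = 0.05: k = 1 + 18 × 0.05/0.95 = 1.95 and √k = 1.40.

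| Assumed ρ | √k | Two-sided error (nominal 5%) | False result favouring IG_B (nominal 2.5%) |
|---|---|---|---|
| 0.01 | 1.09 | 7.0% | 3.5% |
| 0.02 | 1.17 | 9.1% | 4.6% |
| 0.05 | 1.40 | about 15% | 7.7% |
| 0.10 | 1.73 | 24.9% | 12.4% |
| 0.20 | 2.35 | 39.2% | 19.6% |

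Simulated pre/post data gave 15.7%, 25.1% and 39.3% at ρ = 0.05, 0.10 and 0.20. The two-sided error reaches 10% at ρ of about 0.024.

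**Step 3: larger groups.** More children per group make it worse. If all 21 starters per group (18 × 1.15 = 20.7) were analysed, the error would be 17.1% at ρ = 0.05 and 27.5% at ρ = 0.10.

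**Step 4: can a different model repair it?** A test at the level of training groups has 2 − 2 = 0 degrees of freedom. The data cannot estimate ρ between groups or separate programme from group.

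**The case against.** **The size is unknown.** A reader might infer that a false superiority claim is far likelier than 5%. The article does not support that. Without an ICC the excess cannot be fixed: at 0.01 the two-sided error is only 7.0%. A false result in favour of IG_B, the direction of hypothesis (iv), passes 5% only above an ICC of about 0.024, although its excess over the nominal 2.5% is the same in proportion. The same venue, adjacent slots and identical athletics content in two of three weekly sessions could keep the correlation small. This part of the objection stands, and the error must be given as a range.

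**Coaches and classes.** A reader might also infer that each group has its own coach, or that the groups are pre-existing classes. Neither is stated. Section 2.5.1 speaks only of the coaches, and the back-to-back slots are compatible with the same staff serving both groups. Shared staff would remove one source of group-level variance but not peers, slot or test occasion.

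**The wording is partly about groups.** Hypothesis (iii) compares the IG_B group with IG_A, and Section 4 speaks of differences between the two groups. The mismatch therefore lies in hypothesis (iv), the IG_B training objectives and the Discussion.

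**It is a pilot.** The Discussion uses that word and asks for more rigorous trials later. It also ties confirmed superiority to policy recommendations, so the label does not settle the matter.

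**A separate analysis plan could deal with it.** It could restrict the conclusion, but with zero degrees of freedom no model can recover the programme effect. The article itself already fixes both the child-level test and the programme-level claim.

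**Conclusion.** The concern holds in a conditional form. Programme and training group are fully aliased, and the planned test compares two particular training groups. For a programme-level claim, its type I error is above 5% for any positive change-score ICC. At 18 per group it is about 7% to 39% two-sided over assumed ICCs of 0.01 to 0.20, and 3.5% to 19.6% for a false result favouring IG_B, against a nominal 2.5%. These figures assume normally distributed gains and independent group effects of equal variance in the two arms. Where a single ICC would place the trial in this range cannot be learned from the article or from the trial's own data. The point limits what the trial may conclude and should be corrected before results are reported; it does not make the comparison of the two groups worthless.

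**What to change.** 1. In Section 4, state that the ANOVA-RM compares two training groups and that its p-value and confidence interval assume no group-level variance.
2. Report the group-by-time estimate with a sensitivity analysis that multiplies its standard error by √(1 + n·ICC/(1 − ICC)), where n is the number analysed per group, over a range of assumed ICCs named in advance. With 0.02, 0.05 and 0.10, for example, the factors are 1.17, 1.40 and 1.73 at n = 18.
3. Describe any significant result as a difference between two training groups, not as confirmed programme superiority supporting policy recommendations.
4. Add the aliasing to the limitations in the Discussion, and state whether the same coaches lead both groups.

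The sensitivity analysis should not become a rule that allows a superiority claim when the interval at one chosen ICC excludes zero. That ICC cannot be checked with one group per arm, so the rule would not resolve the aliasing. Nor is mixing the two groups in the shared athletics sessions recommended: it conflicts with slots taken by parental availability (Section 2.1) and leaves the Thursday session, the only one that differs, fully aliased.

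The cost is some wording and a few lines of analysis, with no extra children or data. The downside is a wider interval and a more modest conclusion.
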